## Abstract

**Introduction:**

Blepharospasm (BSP) is a functionally disabling disease with a marked impact on the quality of life of patients. Botulinum toxin (BoNT) injections have been recommended as first-line therapy for BSP. However, the clinical benefits of BoNT are temporary with only about 8–10 weeks duration of benefit in most patients with BSP. Per previous case reports, regular use of topical frankincense essential oil (FEO) can achieve significant symptom relief and can decrease the frequency of BoNT injections. This trial will explore whether BoNT combined with regular application of FEO can improve clinical outcomes in patients with BSP.

**Methods and analysis:**

This protocol describes an open-label, randomized controlled trial to be undertaken to evaluate daily topical application of FEO and coconut oil (CO) in patients with BSP. The goal is to enroll 32 patients with BSP who have received immediate BoNT injection in each treatment arm. Only patients who have previously received less than 12 weeks of positive benefits from BoNT therapy will be enrolled. The primary outcome will be the duration of symptom improvement after the intervention with BoNT combined with FEO or CO within the 24-week follow-up period. Symptom improvement is defined as a decrease of one point or more in the Jankovic Rating Scale severity score compared to baseline in patients with BSP. Secondary outcomes will consist of changes in BSP symptom severity, disability, and quality of life from baseline to each time point after the intervention. Safety analysis will be based on the presence of localized skin allergic reactions and adverse events. Outcomes will be assessed at baseline and at weeks 2, 4, 8, 12, 16, 20, and 24 after the therapy begins.

**Discussion:**

This study will provide evidence that FEO therapy is a promising non-invasive therapy that can be easily combined with BoNT injections to improve clinical outcomes in patients with BSP.

**Clinical trial registration:**

https://www.chictr.org.cn/, identifier ChiCTR2400091987.

## Introduction

1

Blepharospasm (BSP), characterized by involuntary bilateral orbicularis oculi muscle spasms, is the most common type of focal dystonia in Asia (1–3). BSP significantly affects the quality of life of patients through motor and non-motor manifestations (3–6). Currently, BSP treatment remains purely symptomatic, owing to its unknown etiology. Oral medications, such as benzodiazepines, anticholinergics, antimuscarinics, and dopaminergic medications, exert temporary benefits, but these vary from patient to patient, generally lack long-term effectiveness, and result in significant side effects (7). Surgical myectomy is invasive and is usually recommended for patients who do not respond to medication (7). Botulinum toxin (BoNT) injections are widely regarded as the gold standard therapy for patients with BSP; however, the clinical benefits of BoNT injections begin to wear off after 8–10 weeks in most patients (8–11). As a result, most patients must receive reinjections after 12 weeks or 4–5 times per year (7). Therefore, there is an urgent need to develop novel adjunct therapies.


We plan to collect data using this novel combination treatment and assess the efficacy and safety of combining topical FEO with BoNT in patients with BSP.

## Methods and analysis

2

### Trial design

2.1

We will conduct a single-centre, open-label, randomised controlled trial. Patients diagnosed with BSP receiving BoNT treatment at our centre will be approached. The protocol follows the Standard Protocol Items: Recommendations for Interventional Trials guidelines (22). Outcomes, including symptom severity, disability, and quality of life, will be evaluated at baseline and at weeks 2, 4, 8, 12, 16, 20, and 24 post intervention. Patients will be asked to complete a self-report questionnaire to document their response to BoNT and the duration of clinical benefits after BoNT treatment. We will recruit only those patients who have received positive benefits from BoNT for less than 12 weeks. We plan to enroll 64 patients and randomly (1:1) assign them to the experimental group (topical FEO combined with BoNT-A injection) or control group [topical coconut oil (CO) combined with BoNT-A injection]. CO will be used as the control because FEO must be diluted 1:1 with CO as the carrier oil (16).

### Study population

2.2

All patients who meet the following inclusion criteria will be included: (1) age 18–70 years; (2) a diagnosis of BSP established according to the published criteria by a senior neurologist (2); (3) a Jankovic Rating Scale (JRS) frequency sub-score of ≥3; (4) documented history of at least three subsequent injection cycles or prospective documentation of one injection cycle of BoNT with less than 12 weeks duration of positive benefits with BoNT by a BoNT-experienced physician (23); (5) written consent obtained from participants. The exclusion criteria include: (1) family history or diagnosis of hereditary dystonia, acquired dystonia, tardive dyskinesia, or functional movement disorders; (2) presence of acute intracranial disease (e.g., stroke, intracranial infection) or history of psychiatric disorders, dementia, epilepsy, multiple sclerosis, tic disorder, Parkinson’s disease, severe traumatic brain injury, or other neurological diseases; (3) significant cognitive impairment; (4) exposure to neuroleptics; (5) contraindication to magnetic resonance imaging (MRI).

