### Safety evaluation

2.5

Based on previous studies, the oral use of frankincense occasionally or rarely causes adverse reactions such as eczema, nausea, aggravation of arthralgia, and gastrointestinal symptoms (20, 36, 37). Topical application of FEO has fewer side effects, predominantly in the form of localized skin allergic reactions (38). All adverse events, including their description, duration, severity, and required treatment, will be documented and treated with care. Any serious adverse events will be immediately reported to the chief investigator and ethics committee of the First Affiliated Hospital of Sun Yat–sen University, and the ethics committee will ultimately determine the termination of the study.

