#### Topical FEO combined with BoNT group

2.8.1

Participants in the experimental group will receive injections of BoNT-A (Hengli, Lanzhou Biological Products Institute, Lanzhou, China; 100 U, diluted in 2 mL saline), using 1 mL syringes and manual targeting techniques. BoNT-A will be routinely administered to the orbicularis oculi muscles at a total of 10 points (5 points on each side). These points encompass the medial and lateral one-third of both the upper and lower eyelids, 2–3 mm from the eyelid margin, and the temporal orbicularis oculi muscle, located 5 mm from the lateral canthus. The corrugator supercilii muscles will receive two injections (one point on each side) located above the inner side of the eyebrows. Additionally, BoNT-A will be injected into the procerus muscle at a central point between the eyebrows. Each point will receive injection of 2.5 U BoNT-A, and the total BoNT-A dosage will be approximately 32.5 U per participant (Figure 2). The injection site and dosage will be adjusted slightly based on the patient’s condition. The next day, participants in the experimental group will begin applying the FEO mixture to the bilateral upper and lower eyelids twice daily, using 0.25 mL of the mixture per application, 0.125 mL for each side. The application will be performed after cleaning the face, and participants will be instructed to gently massage the oil mixture into the skin and rest with their eyes closed to allow absorption.

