#### Topical CO combined with BoNT group

2.8.2

In the control group, the method of injecting BoNT-A and CO will be consistent with that of the experimental group, including site, dosage, and frequency. Participants will be provided with detailed instructions and training on the correct application of the oils, and their adherence to the intervention protocol will be monitored through regular follow-ups. FEO and CO used in the trial are supplied by Aromatics International.^1^

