## Discussion

3

This study will examine whether adding FEO to BoNT therapy can prolong symptom relief. It will also assess whether this combination improves quality of life compared to BoNT alone. In addition, the safety of topical FEO and CO will be evaluated. Sixty-four subjects will be randomized into two groups, with assessments conducted at multiple time points during a 24-week follow-up period. Outcomes will include the duration of symptom improvement, quality of life, and self-rating of response to efficacy, providing evidence of whether FEO therapy is an effective adjunct therapy for the control of BSP symptoms.

However, certain practical issues require clarification. Because FEO has a strong and characteristic odor that cannot be masked even when diluted or sealed, an open-label design was necessary (39). To minimize subjective bias, all assessments will be conducted by two independent blinded evaluators using the same evaluation protocol. Because pure FEO causes irritation when applied directly to the skin, it must be diluted 1:1 with a carrier oil such as CO (16). In this study, CO was chosen as the diluent, but its potential effects on BSP are unknown. Therefore, to control for any influence of CO itself, the control group will receive topical CO alone, applied using the same dosage and massage procedure as in the experimental group.

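### The eligibility list has no criterion on known sensitivity to the study oils or active eyelid inflammation, so patients open to the protocol's own main named risk can be enrolled

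*Protocol article*

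**What the plan says.** Section 2.2 (Study population) opens with "All patients who meet the following inclusion criteria will be included" and gives five inclusion criteria: age, diagnosis, a minimum Jankovic frequency sub-score, a documented short response to botulinum toxin, and consent. The five exclusions cover other dystonias and movement disorders, neurological and psychiatric disease, cognition, neuroleptic exposure and, last, MRI: "5) contraindication to magnetic resonance imaging (MRI".

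On risk, section 2.5 (Safety evaluation) states: "Topical application of FEO has fewer side effects, predominantly in the form of localized skin allergic reactions". The Discussion adds: "Because pure FEO causes irritation when applied directly to the skin, it must be diluted 1:1 with a carrier oil such as CO". The Abstract sets the safety outcome: "Safety analysis will be based on the presence of localized skin allergic reactions and adverse events".

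On exposure, section 2.8.1 has experimental participants "applying the FEO mixture to the bilateral upper and lower eyelids twice daily". For the control arm, section 2.8.2 says "the method of injecting BoNT-A and CO will be consistent with that of the experimental group, including site, dosage, and frequency".

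**The concern.** The criteria screen for unfitness for a pre-treatment scan but not for unfitness for the product under test. A patient who has already reacted to frankincense or coconut oil, or whose eyelid skin is inflamed at screening, meets every criterion as written.

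Two things are at stake. The first is safety: the protocol foresees this harm, and the oil is applied next to the eye. The second is the reading of the safety outcome. If the skin was already inflamed or the patient already sensitised, a local reaction during the trial cannot be cleanly assigned to the product as it would act in patients without that history.

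**Working it through.** The plan gives no figure on this point, so the check is mainly one of text.

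**Step 1. Look for the criterion.**

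| Place | Content | Addresses oil sensitivity or eyelid inflammation? |
|---|---|---|
| 2.2, inclusions 1–5 | Age, diagnosis, Jankovic frequency, toxin history, consent | No |
| 2.2, exclusions 1–2 | Other dystonias and movement disorders; neurological and psychiatric disease | No |
| 2.2, exclusions 3–5 | "3) significant cognitive impairment; (4) exposure to neuroleptics; (5) contraindication to magnetic resonance imaging (MRI" | No |
| 2.7 | Withdrawal and dropout rules | No, these act after entry |
| 2.9 and Table 2, screening | Consent, neurological exam, medical history, eligibility check, MRI, baseline ratings, safety assessment | Not tied to any exclusion |
| 2.11 | Review of harm by a committee | No, this acts after entry |

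The eligibility check in Table 2 can only apply the criteria that section 2.2 lists.

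**Step 2. Set this against the stated risk and exposure.** Section 2.5 names the local allergic reaction as the main side effect. Sections 2.8.1 and 2.8.2 put an oil on the upper and lower lids in both arms. Table 2 marks oil application up to week 24, so the most a participant could receive is about 24 weeks × 7 days × 2 per day = 336 applications, fewer if follow-up ends early under section 2.9.

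**Step 3. Follow each type of patient through randomisation.**
- *Known frankincense sensitivity.* Exposed in the FEO arm only. Reactions add to that arm's rate.
- *Known coconut oil sensitivity.* Exposed in both arms, because the FEO mixture is half coconut oil. Reactions can occur in both arms and can blur the contrast.
- *Eyelid inflammation at entry.* Balanced between arms on average by randomisation, but it adds events of unclear cause to either arm's count.

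**Step 4. Scale.** With 32 participants per arm, one patient is 1/32 = 3.1 percentage points. That is the grain of any rate in this trial. It does not measure how many such patients there are, and the documents give no frequency from which to work that out.

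**The case against.** The strongest reply is that this is a journal article. Its exclusion list is introduced in wording that need not be exhaustive, and a fuller protocol may hold the missing line. The MRI exclusion is also not misplaced, since section 2.4 sends every participant for MRI. The second part stands: nothing is wrong with the MRI criterion. The first part is weaker. Numbered eligibility criteria are not something a protocol article commonly leaves out, and one tied to the product's main named risk would be expected in a list that runs as far as MRI. If it exists elsewhere, saying so settles the point.

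The other reply is that safeguards exist. The irritation statement in the Discussion concerns undiluted oil, and dilution is the stated remedy. Adverse events are documented and treated, participants may withdraw at any time, and a committee reviews harm. Table 2 also has a safety assessment at screening and on Day 0, before the oil starts the day after injection, and the control arm gives a randomised comparator. These points lower the severity and partly answer the attribution problem. They do not close the gap. Recording and treating events comes after exposure. The article does not say that the early safety assessments look at the eyelids, and the only examination Table 2 names is neurological. The comparator does not balance reactions in frankincense-sensitive patients, who meet that oil in one arm only.

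**Conclusion.** The point holds as a gap in the written criteria. Patients with a known reaction to the study oils, or with active eyelid skin inflammation, can be enrolled, exposed to the harm the protocol foresees, and counted in the local-reaction outcome with unclear attribution. It should be fixed, but it does not invalidate the efficacy comparison. Its size is unknown because the documents do not say how common these conditions are.

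A reader might infer three stronger claims that the documents do not support:
- *That such patients are being enrolled.* The text shows only that nothing bars them. A patient or investigator may still decline.
- *That the primary endpoint is biased.* Irritation might increase eyelid closure and so raise the Jankovic severity score, but no section says this. Improvement is also judged against the patient's own baseline, so inflammation already present would be part of that baseline. The route needs new or worse irritation, which is an assumption.
- *That power is lost.* The allowance is 32 − 25 = 7 per arm, but stopping the oil is not the same as losing outcome data. Section 2.10 plans intention-to-treat analysis on all available observations, the dropout rule in section 2.7 concerns other treatments or programmes for blepharospasm, and section 2.9 does not list stopping the oil as a reason to end follow-up. No share of the allowance can be assigned to this gap.

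**What to change.** Reconcile section 2.2 with section 2.5, the Discussion and the safety outcome in the Abstract:

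1. Add an exclusion for known sensitivity to the study oils (frankincense or coconut oil), checked through the medical history that Table 2 already schedules at screening.
2. Have the investigators define how active eyelid skin inflammation at entry is either excluded or recorded at the screening safety assessment. The clinical definition is theirs to set.
3. If either item already stands in the full protocol, state it in section 2.2.

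The first item costs one line and no new procedure. The second may need a brief look at the eyelids that the neurological exam does not clearly include, so it may not be free. Some screen failures will follow, probably few, though the documents give no figure. The required 25 per group is unchanged. Recruitment is planned to 28 February 2027 and the protocol has been amended once already, so an amendment is feasible. Participants already randomised stay in the intention-to-treat population, and the report should say how many entered before and after the change.

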### Objectives and endpoints

2.3

Primary objectives: The study primarily aims to evaluate the clinical effects of topical FEO combined with BoNT injections in patients with BSP. Specifically, we will compare the topical FEO group with the CO group in terms of the duration of symptom improvement, quality of life, and self-rating of response to efficacy during a 24-week follow-up. Symptom improvement is defined as a decrease of one point or more in the JRS severity in the JRS severity score relative to baseline in patients with BSP (24). We hypothesized that, unlike the placebo group, topical FEO combined with BoNT will significantly prolong the duration of symptom improvement, improve patient rating of quality of life, and self-rating of response to efficacy, with acceptable safety at the 24-week follow-up.

The primary endpoint is the duration of symptom improvement over 24 weeks, as defined above.

The secondary endpoint of the study is the percentage change from baseline to different time points in the physician rating of the BSP. This involves motor symptom severity, measured by the JRS (25), the Blepharospasm Severity Rating Scale (BSRS) (26), and the Burke Fahn Marsden’s Dystonia Rating Scales (BFMDRS) (27), and quality of life, assessed by the Blepharospasm Disability Index (BSDI) (25), the Short Form-36 Health Survey (SF-36) (28), and the Cranio-cervical Dystonia Questionnaire (CDQ-24) (29). In addition, patient subjective ratings via the Patient Evaluation of Global Response (PEGR) and the incidence of adverse events will be included (30).

### Data measurements

2.4

All subjects will undergo MRI before the clinical intervention. Demographics, clinical characteristics, and severity of BSP will be recorded using blepharospasm severity scales. The severity of BSP, quality of life, and self-rating of response to efficacy will be evaluated in each patient at baseline and at weeks 2, 4, 8, 12, 16, 20, and 24 after therapy. Moreover, a 5-min standardised video recording of the facial area will be conducted to assess and document the blink rate and duration of sustained eyelid closure (26). In addition, all subjects will be evaluated with non-motor symptom scales at baseline, at weeks 12 and 24 weeks after the intervention, using the Mini-Mental State Examination (MMSE) (31), Hamilton Rating Scale for Anxiety (HAMA) (32), Hamilton Rating Scale for Depression (HAMD) (33), Yale-Brown Obsessive-Compulsive Scale (Y-BOCS) (34), and the Pittsburgh Sleep Quality Index (PSQI) (35). All evaluations applied in the study will be performed at each visit by two evaluators who will be blinded to the clinical information and group assignments of the participants. This will safeguard the objectivity of the evaluation process and ensure the consistency and validity of the assessment results. Figure 1 illustrates the flowchart of the clinical trial procedure, and Table 1 presents an overview of the study.

**Figure 1 fig1:**
[figure not shown]
Clinical trial flow diagram. BoNT-A, botulinum toxin type A; CO, coconut oil; FEO, frankincense essential oil; MRI, magnetic resonance imaging; PEGR, Patient Evaluation of Global Response.

**Table 1 tab1:** Overview of the study.

Item	Description
Study title	Efficacy and safety of combination of frankincense and botulinum toxin in the treatment of blepharospasm: a protocol for a single-centre, open-label, randomized, controlled trial
Study design	A single-centre, open-label, randomized, controlled trial will be conducted in 64 eligible BSP patients, and they will be randomly assigned (1:1) into the experimental group (topical FEO combined with BoNT) and control group (topical CO combined with BoNT) for the 24-week follow-up.
Primary endpoint	The symptom improvement over a 24-week follow-up period.
Secondary endpoints	Intervals between the last and the next BoNT treatments; Improvement rates in motor symptom severity (JRS, BSRS, and BFMDRS scores); Improvement rates in the quality of life (BSDI, SF-36, and CDQ-24 scores); Patient subjective efficacy evaluation (PEGR scores); Incidence of adverse events.
Research intervention(s)/Investigational agent(s)	Daily application topical FEO the day after BoNT injection in the experimental group. Daily topical application of CO the day after BoNT injection in the control group. Outcomes will be collected at baseline and different follow-up time points. BoNT: Hengli. FEO/CO: Aromatics International.
Study population	Patients aged 18 to 70 years whose efficacy duration of BoNT injection was less than 12 weeks.
Sample size	64
Study duration for individual participants	24 weeks

BFMDRS, Burke Fahn Marsden’s Dystonia Rating Scales; BoNT, botulinum toxin; BSDI, Blepharospasm Disability Index; BSP, blepharospasm; BSRS, Blepharospasm Severity Rating Scale; CDQ-24, Cranio-cervical Dystonia Questionnaire; CO, coconut oil; FEO, frankincense essential oil; JRS, Jankovic Rating Scale; SF-36, Short Form-36 Health Survey; PEGR, Patient Evaluation of Global Response.

### Safety evaluation

2.5

Based on previous studies, the oral use of frankincense occasionally or rarely causes adverse reactions such as eczema, nausea, aggravation of arthralgia, and gastrointestinal symptoms (20, 36, 37). Topical application of FEO has fewer side effects, predominantly in the form of localized skin allergic reactions (38). All adverse events, including their description, duration, severity, and required treatment, will be documented and treated with care. Any serious adverse events will be immediately reported to the chief investigator and ethics committee of the First Affiliated Hospital of Sun Yat–sen University, and the ethics committee will ultimately determine the termination of the study.

### Sample size

2.6

The sample size was calculated using the two-sample t-test method in PASS 15 software (NCSS, LLC, Kaysville, Utah, USA), with a two-sided significance level of 0.05 and a power of 0.8. Based on preliminary clinical observations obtained in our center, topical FEO alone was effective in approximately 50% of patients with BSP. This finding, combined with a conservative estimate of efficacy, prompted a reassessment of the required sample size to ensure adequate statistical power. The revision was implemented after trial initiation but prior to completion of participant recruitment, and constitutes an important protocol modification based on internally generated data. To determine the mean and standard deviation (SD) needed for the sample size calculation, we retrospectively analysed data from 61 patients with BSP at our movement disorders clinic who had received standard BoNT-A treatment and met the study’s inclusion criteria. After receiving their last three consecutive BoNT-A injections, these patients experienced clinical benefits for less than 3 months each time, demonstrating consistently unsatisfactory therapeutic effects. The mean duration of clinical benefits was 73.99 days (SD = 14.28). Given that the control group will receive a placebo, there may have been greater variability in the therapeutic effects due to individual response and disease progression; therefore, we decided to round the mean value to 75 days and the SD to 15 (i.e., 75.0 ± 15.0) to ensure robustness in the calculation. In this study, we hypothesized that combining BoNT-A injection with topical FEO would extend the effective duration of symptom relief by 30 days to 105.0 ± 15.0 days. Given an expected effective rate of only 50%, we estimated the mean duration of benefit in the experimental group as 90.0 ± 18.5 days, reflecting a weighted average between responders and non-responders. The resulting sample size calculation indicated N1 = N2 = 25, meaning that 25 participants are required for each group. Considering the participant loss to follow-up, we determined that each group would recruit 32 participants. A professional statistician verified the sample size calculation method. The amended protocol was reviewed and approved by the Ethics Committee of the First Affiliated Hospital of Sun Yat–sen University.

